#### Intensive care arm intervention

Care for the intensive arm is based upon a paradigm of multi-factorial intervention shown to improve mortality in T2DM [41]. Structured education (diabetes education and self-management for ongoing and newly diagnosed diabetes - DESMOND [42]) is initially offered to all patients in the intensive arm with attendance ideally, within the first two months of diagnosis. Sessions are delivered by two trained educators and aim to facilitate lifestyle changes in relation to dietary habits, physical activity levels, smoking cessation and glucose monitoring. Those participants who are unable, or decline the opportunity to attend the structured education programme are offered one-to-one advice with a dietitian. All volunteers are offered a glucometer, and encouraged to maintain a reflective diary. On-going professional support is provided in the first year through an individualised peripatetic clinic offering two monthly visits from a diabetes specialist nurse or physician. Ultimately, participants are encouraged to self-manage their diabetes by identifying personalised goals which facilitate individualised behaviour and lifestyle change.

Patients without specific contra-indications are advised to take aspirin 75 mg orally and prescribed lipid lowering therapy (simvastatin 40 mg once daily) if total cholesterol concentration exceeds 3.5 mmoll^-1^. An individualised, stepwise approach to management according to specified algorithms is adopted to ensure optimisation of hypertension, dyslipidaemia and hyperglycaemia according to protocol-driven targets using medication within existing licensed indications (table 2). Recommended drug choices take in to account treatment efficacy, side-effects and cost, the main priority being achievement of treatment targets whilst maintaining flexibility and low rates of adverse events. The approach is deliberately pragmatic with the final decision on choice of medication determined by the health care professional and patient. Treatment targets for the intensive care arm are based on complex interventions with proven efficacy in T2DM; HbA1c <7.0% with initiation of treatment at 6.5%, blood pressure <130/80 mmHg, and total cholesterol <3.5 mmoll^-1 ^[41]. After the first year, community visits are extended to every four months but continue to be guided by protocol driven blood pressure, HbA1c%, and lipid targets.

At annual visits (V1-V4 table 1) interim outcome measures and additional biomedical assessments are performed, including urinary albumin creatinine ratio (ACR), electrocardiography and thyroid function tests. This visit includes a standardised foot examination incorporating a vascular doppler assessment, ankle-brachial pressure indices and monofilament neuropathy testing. A stereoscopic digitalised retinal examination is performed and independently verified by operators blinded to the participants study group allocation.

The intensive treatment protocol is externally moderated by the trial steering committee and specifically designed to achieve HbA1c%, blood pressure and serum lipid targets below current national recommendations.

### Endpoints and outcomes

#### Primary endpoint

The primary endpoint is reduction in modelled coronary heart disease at five years using the United Kingdom Prospective Diabetes Study (UKPDS CHD) risk equation [43]. The UKPDS CHD risk engine has the advantage of being diabetes specific and incorporates an adjustment for the effects of south Asian ethnicity when calculating CHD risk. It has recently been shown to be as accurate as other CHD risk assessment tools in T2DM and has been validated for the effects of ethnicity [43].

#### Secondary and intermediate outcomes

Secondary outcomes of ADDITION-Leicester are a microvascular complication composite of diabetic retinopathy, neuropathy or microalbuminuria, a vascular atherosclerosis surrogate (carotid femoral pulse wave velocity), all cause mortality (assessed by participants tagging with the Office for National Statistics), non-fatal cardiovascular events, hospitalisation, health service cost and quality of life indicators.

Intermediate outcomes are measured annually in the intensive care arm and at one, three and five years in the routine care arm (table 1). These include HbA1c%, blood pressure, total cholesterol, microalbuminuria, self-reported hypoglycaemic episodes, weight, physical activity, ankle-brachial pressure indices and smoking status.

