### The ADDITION study

As a result of such critical uncertainties the UK National Screening Committee currently recommend a targeted rather than universal approach, with screening confined to groups at particularly high risk of T2DM [23,24]. There is some evidence that UK general physicians are increasingly carrying out opportunistic or planned community screening of their patients [25,26]. Implementation of the National Health Service (NHS) vascular check programme recommending glucose testing for 40-70 year olds will undoubtedly further increase T2DM screening activity in the UK [27].

Priority should be directed towards developing a robust evidence base informing national policy and protecting against indiscriminate, poorly coordinated screening programmes. The results of randomised controlled trials among screen-detected cases with outcomes assessing vascular complications, health satisfaction, process of care indicators and cost are vital to this process.

ADDITION (Anglo-Danish-Dutch Study of Intensive Treatment in People with Screen Detected Diabetes in Primary Care) is a multi-centred randomised controlled trial evaluating the effectiveness of multi-factorial treatment on risk of cardiovascular disease events among over 2500 patients with screen-detected diabetes [28-30]. ADDITION-Leicester contributes to this multi-centre study but is also a stand-alone trial evaluating screening within a UK multiethnic group and quantifying the efficacy of optimised treatments on modelled cardiovascular risk over five years.

This paper describes the aims and methods of both screening and intervention phases of the ADDITION-Leicester study.

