### Statistical methods and power calculation

Assuming a prevalence of screen-detected diabetes of 4.5%, we calculated a target of 7,000 (30% (2,100) South Asians) volunteers over three years sufficient to identify a screen-detected T2DM cohort (n = 225) demonstrating a 6% difference (80% power, alpha 0.05) between routine and intensive groups at one year assuming an intra cluster correlation coefficient of 0.14 and allowing for a loss to follow-up of 15%.

The benefits of screening and intensive treatment will be assessed using an intention to treat and allowing for clustering of patients by practice. The UKPDS CHD score at 5 years will be compared along with all secondary outcomes by treatment group, adjusting for differences in baseline variables. Estimates will be presented with 95% confidence intervals to reflect uncertainty in estimations. Sensitivity analysis assuming a range of outcomes for non-completers will be informed by baseline data. The primary perspective for the cost analysis will be the health service, with personal costs as a secondary perspective. The costs of intensive intervention will be compared with unit change in health utility at one year. Costs at one year and future costs derived from existing data will be compared with modelled risk of death and cardiovascular events, with appropriate sensitivity analysis. The cost of screening and the screening plus intensive treatment will be compared with changes in health utility from questionnaire data.

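### The only observed cardiovascular event outcome counts non-fatal events alone, so a first event that is fatal counts in no cardiovascular outcome

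*Protocol article*

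**What the plan says.** Under Secondary and intermediate outcomes, the protocol article names "all cause mortality (assessed by participants tagging with the Office for National Statistics), non-fatal cardiovascular events, hospitalisation" as separate items. The other secondary outcomes are a microvascular composite, pulse wave velocity as a surrogate, health service cost and quality of life. None of them counts cardiovascular deaths or combines fatal with non-fatal cardiovascular events.

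Under Primary endpoint, the article states: "The primary endpoint is reduction in modelled coronary heart disease at five years". That is a calculated score and not a count of events.

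Under Statistical methods and power calculation, it commits to a between-arm comparison of every item in the list: "The UKPDS CHD score at 5 years will be compared along with all secondary outcomes by treatment group".

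**The concern.** The restriction to non-fatal events is a stated definition, not a detail left for another document. It has two consequences.

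- **Lost events.** An infarction or stroke that kills as the first event is as much a cardiovascular event as one that is survived, yet it is not counted as one. In a cohort of a few hundred patients, every event matters for precision.
- **Conditioning on survival.** To count, a patient must survive the event. The section on the intensive care arm bases that arm on an approach reported to improve mortality, so on the trial's own rationale death is something treatment may change. If treatment alters how often an event is fatal, the non-fatal count mixes the prevention of events with a change in who survives them.

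All-cause mortality does not fully repair this. It mixes cardiovascular with other deaths. Nor can the two outcomes be added to give first cardiovascular events, because one patient may have a non-fatal event and die later.

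**Working it through.** The article gives no event rate, event count or power for this outcome, so there is no figure of its own to reproduce.

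**Inputs from the article:** 345 cases identified and a mean follow-up of 5 years (Funding and timescale); practices randomised 1:1 (Phase 2).

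**Assumptions, not in the article:** five-year first non-fatal cardiovascular events in 6-8% of patients; fatal first cardiovascular events in 1.5-3%.

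**Step 1: events and precision.** Events = 345 × risk. The increase from adding fatal first events is fatal risk / non-fatal risk. With rare events the standard error of the log relative risk is roughly proportional to 1/√events, so the interval narrows by 1 − 1/√(1 + increase).

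| Non-fatal | Fatal | Non-fatal events | All first events | Increase | Narrowing |
|---|---|---|---|---|---|
| 6% | 1.5% | 20.7 | 25.9 | 25% | 11% |
| 6% | 3% | 20.7 | 31.1 | 50% | 18% |
| 8% | 1.5% | 27.6 | 32.8 | 19% | 8% |
| 8% | 3% | 27.6 | 38.0 | 38% | 15% |

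The range over all four pairings is 19-50% more events and about 8-18% narrower. Clustering is ignored; the relative narrowing is unchanged if the design effect is the same for both outcomes.

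**Step 2: when is the comparison distorted?** A constant-hazard model over 5 years was used with three causes: non-fatal first event, fatal first event and other death. Cumulative incidence of a cause = (its hazard / total hazard) × (1 − exp(−5 × total hazard)). Further assumptions: control-arm cardiovascular risk 4-12%, fatal share of first events 15-40%, other-death hazard 0.6% a year.

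- *Same effect on fatal and non-fatal events (hazard ratio 0.8 for both).* The non-fatal and total risk ratios agree, at 0.80-0.81. Nothing is distorted; only events are lost. At 8% risk and 345 patients, 3.7-9.8 of 24.6 events are missed.
- *Removal from risk only (non-fatal hazard unchanged, fatal and other-death hazards halved).* The non-fatal risk ratio is 1.01-1.02, a shift of 1-2%.
- *Treatment also makes events less often fatal (8% risk, total hazard ratio 0.8, total risk ratio 0.81).* The non-fatal risk ratio is 1.08 if the fatal share is 40% in routine care and 20% in intensive care, 1.04 for 30% v 10%, 1.02 for 25% v 5%, and 1.21 for 40% v 10%.

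**Step 3: how large must that change be?** With a total hazard ratio of 0.8, the non-fatal hazard is higher under intensive care only if the fatal share there falls below 1 − (1 − routine share)/0.8. For the pairings in Step 1:

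- 6% + 3%: share 3/9 = 33%; threshold 1 − 0.667/0.8 = 17%.
- 8% + 3%: share 3/11 = 27%; threshold 1 − 0.727/0.8 = 9%.
- 6% + 1.5%: share 1.5/7.5 = 20%; threshold 1 − 0.80/0.8 = 0, so not possible.
- 8% + 1.5%: share 1.5/9.5 = 16%; threshold below 0, so not possible.

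**The case against.** The strongest reply is that fatal events are not lost to the trial. All-cause mortality is in the same list and will be compared by arm. If treatment turned fatal events into survived ones, the report would show more non-fatal events beside fewer deaths. This stands in part: it guards against misreading, although non-cardiovascular deaths dilute the signal. All-cause mortality also avoids misclassified causes of death, which is a fair reason to prefer it.

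A second reply is that an article condenses a fuller plan. That holds for the handling of competing deaths and the reporting of components, and their absence is not held against the article. It does not hold for the definition itself, which the article states.

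A third reply is that this is one secondary outcome with few events and would not be decisive even with fatal events added. That also stands, and it limits the weight of the point.

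A reader might go further and infer that the non-fatal count will reverse the apparent treatment effect. The documents do not support this. Reversal needs an effect on lethality that differs from the effect on non-fatal events, and nothing in the article indicates one of the required size. Even in a constructed case with 12 non-fatal and 4 fatal events under routine care against 14 and 2 under intensive care, the non-fatal relative risk is 14/12 = 1.17. Its 95% interval is about 0.56-2.45 with about 172 patients per arm and clustering ignored. The total relative risk is 16/16 = 1.00, so no overall benefit is reversed.

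**Conclusion.** The point holds as a limited one. By the stated definition, a fatal first cardiovascular event counts in no cardiovascular outcome. The loss of the fatal share needs no assumption about treatment. Its size does rest on assumption, because the article gives no rates: under the ranges above, including fatal events gives 19-50% more events and an interval about 8-18% narrower. Distortion of the comparison is conditional on different effects on fatal and non-fatal events.

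A reader might also infer that the result cannot be set beside that of the parent multi-centre trial, described as "evaluating the effectiveness of multi-factorial treatment on risk of cardiovascular disease events". The article does not give that trial's endpoint definition, so no such conclusion can be drawn.

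The primary endpoint and the sample size do not depend on this outcome. The change is a cheap improvement to a secondary outcome.

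**What to change.** Define the secondary outcome as first fatal or non-fatal cardiovascular event. Report non-fatal events and cardiovascular deaths as components, and treat non-cardiovascular death as a competing event. Keep all-cause mortality as it is.

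Take cause of death from the national mortality tagging already in place. The article says that tagging assesses all-cause mortality and does not say that cause is returned, so the sponsor should confirm this first. If cause is not available, report a composite of non-fatal cardiovascular event or all-cause death beside the non-fatal count. This removes the conditioning on survival, at the price of including non-cardiovascular deaths.

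The cost is a change of outcome wording, a small amount of cause-of-death coding and some risk of misclassified cause. No visits or patients are added.

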#### Screening outcomes

Response and attendance characteristics (obtained from MPLs) will provide an objective assessment of screening within the invited population. The programme is of sufficient size to enable the feasibility and complexities of screening to be stratified by ethnicity and socio-economic status. Outcomes will include the number of individuals responding to first and second mailers, presenting for screening, and subsequently diagnosed with T2DM or IGR. Metabolic dysfunction, cardiovascular risk, psychological status and self-perceived health in newly diagnosed T2DM and IGR will be determined. Population effects of screening will be determined via Office of National Statistics (ONS) mortality tagging and self-report health questionnaires five years after screening. Response and attendance rates will also be compared with previous population T2DM screening studies to enable specific conclusions to be drawn about the ADDITION-Leicester population [25,29].

#### Health economic outcomes

The economic analysis will establish the NHS costs of Phase 1 (screening) for T2DM and IGR from a patient and health service perspective. The cost-effectiveness of multifactorial intervention within our population of screen-detected cases will be determined from a health service perspective. Personal patient costs to attend the assessments (screening and as part of the trial) are collected at each visit. Health service use is assessed using data on consultations with healthcare professionals, hospitalisations and medications in the twelve months leading up to annual review.

### Statistical methods and power calculation

Assuming a prevalence of screen-detected diabetes of 4.5%, we calculated a target of 7,000 (30% (2,100) South Asians) volunteers over three years sufficient to identify a screen-detected T2DM cohort (n = 225) demonstrating a 6% difference (80% power, alpha 0.05) between routine and intensive groups at one year assuming an intra cluster correlation coefficient of 0.14 and allowing for a loss to follow-up of 15%.

The benefits of screening and intensive treatment will be assessed using an intention to treat and allowing for clustering of patients by practice. The UKPDS CHD score at 5 years will be compared along with all secondary outcomes by treatment group, adjusting for differences in baseline variables. Estimates will be presented with 95% confidence intervals to reflect uncertainty in estimations. Sensitivity analysis assuming a range of outcomes for non-completers will be informed by baseline data. The primary perspective for the cost analysis will be the health service, with personal costs as a secondary perspective. The costs of intensive intervention will be compared with unit change in health utility at one year. Costs at one year and future costs derived from existing data will be compared with modelled risk of death and cardiovascular events, with appropriate sensitivity analysis. The cost of screening and the screening plus intensive treatment will be compared with changes in health utility from questionnaire data.

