**Methods:**

ADDITION-Leicester consists of community-based screening and intervention phases within 20 general practices coordinated from a single academic research centre. Screening adopts a universal diagnostic approach via repeated 75g-Oral Glucose Tolerance Tests within an eligible non-diabetic population of 66,320 individuals aged 40-75 years (25-75 years South Asian). Volunteers also provide detailed medical and family histories; complete health questionnaires, undergo anthropometric measures, lipid profiling and a proteinuria assessment. Primary outcome is reduction in modelled Coronary Heart Disease (UKPDS CHD) risk at five years. Seven thousand (30% of South Asian ethnic origin) volunteers over three years will be recruited to identify a screen-detected T2DM cohort (n = 285) powered to detected a 6% relative difference (80% power, alpha 0.05) between treatment groups at one year. Randomisation will occur at practice-level with newly diagnosed T2DM cases receiving either conventional (according to current national guidelines) or intensive (algorithmic target-driven multi-factorial cardiovascular risk intervention) treatments.

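### The 80% power is stated only for a one-year difference while the primary endpoint is at five years, and the abstract and the statistical section disagree on the sample size and the effect scale

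*Protocol article*

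**What the plan says.** The Primary endpoint section reads: "The primary endpoint is reduction in modelled coronary heart disease at five years", using the UKPDS risk equation. The statistical section sets the main comparison at the same time: "The UKPDS CHD score at 5 years will be compared along with all secondary outcomes by treatment group", with adjustment for baseline differences.

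The power calculation is stated twice, both times for one year:

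| Place | n | Effect | Time point | Also stated |
|---|---|---|---|---|
| Abstract, Methods | 285 | "powered to detected a 6% relative difference (80% power, alpha 0.05) between treatment groups at one year" | one year | – |
| Statistical methods and power calculation | 225 | "demonstrating a 6% difference (80% power, alpha 0.05) between routine and intensive groups at one year assuming an intra cluster correlation coefficient of 0.14" | one year | ICC 0.14, loss to follow-up 15%, prevalence 4.5% of 7,000 screened |

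The sentence in the statistical section names neither the outcome nor the scale of the 6%. No mean risk, SD or control-arm value appears anywhere in the article. The trial has 20 practices, randomised 1:1 (Phase 1 and Phase 2 sections), and 345 cases had been identified when screening ended (Funding and timescale).

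**The concern.** The only power claim belongs to a contrast that the article does not call primary. Nothing carries it to year five: there is no five-year effect, SD, intracluster correlation or attrition figure. The 15% loss accompanies a one-year calculation and need not hold at five years.

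The two statements share alpha, power and time point, and so appear to be one calculation, yet n differs and the effect is called relative in only one of them. The scale matters: 6% of mean risk and 6 percentage points of risk can be very different effects. A reader of the abstract could take a null five-year result as evidence against a 6% relative effect, and no calculation in the article supports that inference.

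**Working it through.** **Inputs.** From the article: alpha 0.05, power 80%, ICC 0.14, 20 practices, 1:1 allocation, n = 225 or 285, loss 15%, prevalence 4.5% of 7,000, 345 cases identified. Assumed here: two-sided test, 10 practices per arm, equal practice sizes, normal critical values.

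**Step 1. The stated n.** The expected yield is 7,000 × 0.045 = 315, and 315 × 0.85 = 268. If 225 is meant after loss, the number to identify is 225 / 0.85 = 265. None of these is 285. Without an SD, neither 225 nor 285 can be reproduced forwards, so the formula is solved backwards.

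**Step 2. Detectable effect.** With m = N/20:

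- design effect = 1 + (m − 1) × 0.14
- effective N = N / design effect
- detectable difference in SD units = (1.960 + 0.842) × √(4 / effective N)

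For 191 completers (225 × 0.85 = 191.25): m = 9.56, design effect = 1 + 8.56 × 0.14 = 2.20, effective N = 191.25 / 2.20 = 87, difference = 2.802 × √(4/87) = 0.60 SD.

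| N analysed | Design effect | Effective N | Detectable | SD/mean needed for 6% relative | SD needed for 6 points |
|---|---|---|---|---|---|
| 191 (225 less 15%) | 2.20 | 87 | 0.601 SD | 0.100 | 10.0 |
| 225 | 2.44 | 92 | 0.583 SD | 0.103 | 10.3 |
| 242 (285 less 15%) | 2.56 | 95 | 0.576 SD | 0.104 | 10.4 |
| 285 | 2.86 | 100 | 0.561 SD | 0.107 | 10.7 |
| unlimited per practice | – | 20 / 0.14 = 143 | 0.469 SD | 0.128 | 12.8 |

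The last two columns are 0.06 and 6 divided by the detectable difference. Using t on 18 degrees of freedom raises 0.601 to 0.635 and 0.576 to 0.609.

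**Step 3. What each reading needs.** Read as absolute, 191 completers with an SD of 10 points have 79.9% power for 6 points. Read as relative, 80% power needs an SD of about 10% of mean risk, and at most 12.8% however many patients each practice supplies. For illustration only, with assumed SD/mean and no baseline adjustment, 242 completers have 31% power for a 6% relative effect at SD/mean 0.2, 16% at 0.3 and 8% at 0.5.

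**Step 4. Baseline adjustment.** If adjustment reduces the SD by √(1 − r²) and leaves the ICC unchanged, the baseline correlation needed to bring SD/mean down to 0.104 is r = √(1 − (0.104 / CV)²), where CV is the unadjusted SD/mean. This gives 0.85 at CV 0.2, 0.94 at 0.3 and 0.98 at 0.5.

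**Step 5. Five years.** Assume 25–35% loss from the 345 cases identified. That leaves 259 to 224 analysed, with design effects 2.67 to 2.43 and effective N 97 to 92. The detectable difference is 0.57 to 0.58 SD before baseline adjustment.

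**The case against.** The strongest reply is that the article gives no SD or mean, so nobody can show from it that a 6% relative effect is beyond the design. That stands: Step 3 yields a condition, not an impossibility.

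A second reply is that the planned analysis adjusts for baseline, so the SD that matters is a residual one and the illustrative powers describe an analysis the article does not specify. This also stands in part. Adjustment could be enough at SD/mean 0.2, but at 0.3 or more the correlation needed is very high unless adjustment also lowers the ICC.

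Third, a reader might infer from the time mismatch that the five-year analysis is underpowered. The document does not support this. The five-year effect could be larger or smaller than the one-year effect, and under the assumed losses the 345 cases give 0.57–0.58 SD, no worse than the 0.60 SD implied by 225 less 15%.

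Finally, a journal article may leave details such as practice-size variation or the choice of critical values to a fuller document, and their absence is no fault here. That does not excuse a calculation that is printed at a time point other than the primary one and printed in two conflicting forms.

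**Conclusion.** The point holds in three parts. First, power is stated for one year only, so the article states none for its five-year primary analysis; this needs no outside figure. Second, the two statements conflict on n (285 against 225), and one calls the effect relative while the other gives no scale. Third, under equal practice sizes, 20 practices and ICC 0.14, a 6% relative effect has 80% power only if the SD of the analysed outcome, after any baseline adjustment, is about 10% of mean risk.

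So small an SD seems unlikely for a risk score in adults of both sexes, several ethnic groups and ages 25–75, but that is a judgement. The close fit of 6 points with an SD near 10 suggests that the word *relative* may be the slip. A reader might conclude that the calculation makes sense only on the absolute scale; without a stated mean or SD, the document does not settle it.

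**What to change.** 1. Reconcile n (225 or 285) between the abstract and the statistical section, and say whether it is before or after the 15% loss.
2. State the outcome and scale of the 6% difference. Correct *relative* in the abstract, or justify it with the assumed mean and SD of UKPDS CHD risk.
3. Give the power or detectable difference for the five-year primary endpoint, from the 345 cases identified (or the number of these who entered the trial), 20 practices, ICC 0.14 and a stated five-year attrition. At an assumed 25–35% loss this is about 0.57–0.58 SD before baseline adjustment.
4. Label the one-year power as applying to an interim contrast.

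The cost is rewording the abstract and one paragraph. No extra patients and no change of analysis are needed. The stated figure may turn out less favourable than the present one.
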